**Figure 1 f1:**
[figure not shown]
Diactive-1 app interface and main navigation screens.

#### Development of the study

2.8.1

The project was conceived by a multidisciplinary team comprising physicians, nutritionists, psychologists, physiotherapists, educators, exercise professionals, and innovation specialists. The Diactive-1 web platform and mobile application were developed by software engineers and graphic designers in collaboration with the multidisciplinary research team. Previous usability and preliminary effectiveness findings informed the refinement of Diactive-1 (v2.0), including updates to the training algorithm, educational content, and user-engagement features.

#### Content and use of the usual clinical care group

2.8.2

Participants allocated to the usual care group will receive standard multidisciplinary diabetes management within the public healthcare system, including insulin therapy, glucose monitoring, structured diabetes education, and routine follow-up visits. Habitual physical activity, such as school-based physical education or pre-existing sports participation, will be permitted throughout the study. After completion of the 12-week post-intervention assessment and the subsequent 7-day post-visit diabetes-related data collection, participants in the usual care group will be offered access to the Diactive-1 mHealth application. Any clinically indicated modifications to diabetes treatment or technology will be made at the discretion of the treating clinician and documented accordingly.

#### Content and use of the intervention group

2.8.3

Participants will use the Diactive-1 app (v.2.0), which delivers resistance-training programs that can be performed in any setting (e.g., home, park, or school). Programs are stratified into three levels (i.e., low [≤ 20^th^], medium [21^st^–79^th^], and high [≥80^th^]) according to baseline handgrip-strength percentiles derived from age- and sex-specific European FitBack^©^ reference values for children and adolescents (30). The training algorithm incorporates progressive overload within each level. Intensity increases across levels through greater technical complexity, progressing from less functional to more functional movement patterns, while volume increases through prespecified changes in the number of exercises per session, sets, repetitions, and recovery intervals.

Low- and medium-level sessions include five exercises arranged in a pyramidal sequence alternating body segments to reduce localized fatigue and support adaptation during the first technical progression across levels (i.e., core, lower limb, upper limb, lower limb, core). High-level sessions include six exercises grouped by body segment to increase internal load (i.e., two core, two upper-limb, and two lower-limb exercises). Within each session, exercises with similar movement patterns will not be repeated. Inter-exercise recovery remains constant throughout the program (40 seconds), while inter-set recovery increases across training levels (20, 25, and 30 seconds) to support tolerance to increasing neuromuscular demands. Load progression is organized into sequential ten-session blocks, beginning with an increase in repetitions (from 6–8 to 12–15) per set. After participants reach the upper repetition range, the number of sets per exercise increases (from 3 to 4), with a temporary reduction in repetitions to preserve effort tolerance; repetitions are then progressively increased within the new set structure. This progression applies to both classic and circuit training modes. Participants may also select a short-duration Tabata mode, consisting of repeated sets alternating with 20 seconds of exercise, during which they perform as many repetitions as possible, with 10 seconds of recovery. Once all programmed exercises within a set block are completed, the block ends and the sequence restarts until the prescribed number of blocks is completed. **Figure 2** shows the programmed load progression for each training modality.

**Figure 2 f2:**
[figure not shown]
Programmed progression of training volume and recovery intervals for the classic, circuit, and Tabata resistance-training modalities in Diactive-1: **(A)** classic and circuit training; **(B)** Tabata training.

Diactive-1 (v.2.0) requires participants to enter glucose values before and after each training session. These values are used to provide educational messages based on CGM readings (18). In this updated version, additional messages are provided for participants using the Medtronic MiniMed 780G automated insulin delivery system (19), reflecting its frequent use in the participating Spanish clinical settings. These messages are intended to support type 1 diabetes self-management and the safe completion of the corresponding resistance-training session. In general, messages for hyperglycemia focus on insulin-dose adjustment, while messages for hypoglycemia focus on rapid-acting carbohydrate intake according to the participant’s body mass. Specifically, training is not permitted when glucose is <70 mg/dL (<3.9 mmol/L) or when glucose is >270 mg/dL (>15.0 mmol/L) with ketone levels >1.5 mmol/L. Conversely, when interstitial glucose is >270 mg/dL (>15.0 mmol/L), trending upward, and ketone levels are <1.5 mmol/L, the app provides short continuous aerobic exercise sessions to support insulin bolus–mediated correction of hyperglycemia before reassessing eligibility for resistance training. As a further update, Diactive-1 (v.2.0) includes “Did you know?” loading-screen messages summarizing findings from scientific studies linking muscular strength with health benefits, aiming to make research evidence accessible to youth with type 1 diabetes.

Diactive-1 (v2.0) incorporates two gamification components designed to support user engagement in health-related behavior change. First, a point- and level-based progression system awards XP for completed weekly sessions, with additional XP for sustained streaks. Consecutive training days are displayed as flame icons, and accumulated XP allows participants to progress through user levels and appear in a nickname-coded ranking stratified by biological sex and age group. These level-feedback (31), and streak-based systems (32), are recognized gamification strategies used in health and physical activity mHealth interventions. Second, an achievement system unlocks 80 badges classified as common, rare, or epic. This system corresponds to the achievement attribute of gamification, which has been identified as a relevant motivational component in healthcare contexts (33). To further enhance usability and engagement, Diactive-1 (v.2.0) can be configured in either Spanish or English. In addition, participants may link their Spotify profile to the app, allowing them to listen to their own music during training sessions. These features are intended to support accessibility, personalization, and user experience during the intervention.

During all sessions, a randomly assigned 3D avatar (i.e., either a boy or a girl) guides participants by demonstrating the exercises. The avatar is accompanied by narrated instructions, including technique cues, transitions for unilateral exercises, and rest-period duration, to support safe training. **Figure 3** illustrates the sequence of a Diactive-1 (v2.0) training session.

**Figure 3 f3:**
[figure not shown]
Sequence of the Diactive-1 training session, including pre-exercise glucose assessment, safety recommendations, exercise selection and execution, post-exercise glucose assessment, gamification, and perceived exertion reporting.

#### Intervention participation measurement

2.8.4

Intervention participation will be assessed through app access data, and completed sessions will be defined as sessions that are started and fully completed; the type of session, the number of exercises performed, and the number of sets and repetitions will be recorded. At the end of each session, participants will report their perceived exertion using the modified Borg scale from 0 (“not intense”) to 10 (“extremely intense”) (34). Thus, participation data will capture both session completion and the perceived intensity of each completed session for all participants. Every Thursday, participants will receive a notification indicating the number of sessions completed that week, allowing three remaining days within the Monday-to-Sunday period to meet ADA recommendations (20).

These measures will be supplemented by mean and maximum heart rate recorded using the Polar Verity Sense monitor (Polar Electro, Kempele, Finland) in participants recruited from four randomly selected hospitals. Because of resource constraints, heart-rate monitoring will be limited to this subsample and will provide complementary objective information rather than define intervention exposure. Exercise execution quality will not be formally assessed; however, standardized tutorials, 3D exercise demonstrations, and narrated technique cues will be provided to support correct and safe execution.

### Primary outcome

2.9

The primary outcome will be the change in age- and sex-standardized handgrip strength z-score from baseline to 12 weeks. Handgrip strength was selected as the primary outcome because it is a feasible, standardized, and clinically practical indicator of muscular fitness that can be assessed consistently across participating hospitals and showed a significant between-group improvement in the previous single-center Diactive-1 trial (10). The trial will assess whether participants allocated to the intervention group show greater improvement in handgrip strength z-score than those allocated to the usual care group. Handgrip strength will be measured with the Takei III Smedley Type 297 digital dynamometer (Takei Scientific Instruments, Niigata, Japan), following The Youth Fitness International Test (YFIT) (35). Each participant will perform two maximal trials alternately with each arm, and the best value for each hand will be recorded. The average of the best right- and left-hand values will be used as the absolute handgrip strength value. Handgrip strength will then be standardized using FitBack^©^ sex- and age-specific reference values to obtain z-scores (30). Absolute handgrip strength in kilograms will be reported as a secondary outcome. This approach is supported by preliminary Diactive-1 trial findings showing a significant between-group improvement in handgrip strength z-score at 12 weeks (23).

### Secondary outcomes

2.10

Secondary outcomes assessed in Diactive-1 are summarized in **Table 1**. Secondary outcomes are organized hierarchically in: key secondary outcomes (i.e., glycemic-stability parameters and insulin requirements); descriptive or contextual outcomes (i.e., sociodemographic information, diabetes-related clinical characteristics, anthropometric parameters, pubertal maturation, intervention engagement, and barriers to physical activity); and exploratory or hypothesis-generating outcomes, including cardiovascular biomarkers and lipid profile; lifestyle-related outcomes (i.e., 24-hour movement behaviors and adherence to the Mediterranean diet); physical-domain outcomes (i.e., self-reported physical fitness and physical literacy); mental and psychosocial outcomes (i.e., psychological assessments, health-related quality of life, and screening for eating disorders); and implementation-related outcomes intended to explore usability, acute glycemic responses, and potential dose-response relationships (i.e., app usability and data recorded by the Diactive-1 app).

**Table 1 T1:** Summary of the variables examined in the randomized clinical trial.

Primary outcome	Measurement	Tool
Handgrip strength	Directly: Objectively	- Takei III Smedley Type 297 digital dynamometer. - Age- and sex-standardized z-score calculated using FitBack^©^ reference values.
Secondary Outcome	Measurement	Tool
Glycemic stability	Indirectly: - Objectively	- CGM downloads. (without brand distinction)
Insulin requirements	Indirectly: - Objectively - Self-reported	- Insulin pump downloads. - Smart-pen logs. - Insulin records from participants using CGM. (without brand distinction)
Cardiovascular biomarkers and lipid profile	Directly: - Objectively	- Laboratory testing at each hospital’s central laboratory. (standardized protocols)
Anthropometric parameters	Directly: - Objectively	- Height: SECA 213 stadiometer. - Weight: SECA electronic scale.
Maturity status	Indirectly: - Objectively	- Peak height velocity: Moore’s equation. - Tanner scale.
Self-reported fitness	Subjectively: - Self-reported	- International Fitness Scale (IFIS)
Physical literacy	Subjectively: - Self-reported	- Spanish Perceived Physical Literacy Instrument (S-PPLI)
24-Hour Movement Patterns	Subjectively: - Self-reported	- Physical activity: Physical Activity Questionnaire for Children (PAQ-C), or Physical Activity Questionnaire for Adolescents (PAQ-A). - Screen time: selected items from the Health Behavior in School-aged Children (HBSC) questionnaire. - Sleep: selected items from the Pittsburgh Sleep Quality Index (PSQI).
Barriers to physical activity	Subjectively: - Self-reported	- Physical Activity Barriers Scale-1 (PABS-1).
Sociodemographic information (baseline only)	Subjectively: - Self-reported	- Family Affluence Scale III (FAS III)
Psychological assessments	Subjectively: - Self-reported	- CUBE questionnaire.
Quality of life for youth	Subjectively: - Self-reported	- DISABKIDS questionnaire. - KIDSCREEN-10 Index.
Quality of life for families	Subjectively: - Self-reported	- DISABKIDS questionnaire for parents. - KIDSCREEN-10 Index for parents.
Mediterranean diet	Subjectively: - Self-reported	- Mediterranean Diet Quality Index for Children and Adolescents (KIDMED).
Eating disorders	Subjectively: - Self-reported	- Sick, Control, One, Fat, Food questionnaire (SCOFF)
App usability users	Subjectively: - Self-reported	- User Version of the Mobile Application Rating Scale (uMARS).
App usability experts	- Expert-rated	- Mobile Application Rating Scale (MARS).
Diactive-1 app parameters	Directly: - app-recorded	Diactive-1 (v.2.0) app: - Session date and time. - Training type. - Pre- and post-session glucose levels and trend arrows. - Hypoglycemia events. - Mean and maximum heart rate, when available in the heart-rate monitoring subsample. - Satisfaction and perceived exertion levels. - Number of exercises, sets, and repetitions. - Recovery times.

#### Glycemic stability

2.10.1

Glycemic parameters, including CGM wear time, mean glucose, glucose management indicator (GMI), time well above range (%TwAR; >250 mg/dL [>13.9 mmol/L]), time above range (%TAR; 180–250 mg/dL [10.1–13.9 mmol/L]), time in range (%TIR; 70–180 mg/dL [3.9–10.0 mmol/L]), time below range (%TBR; 54–70 mg/dL [3.0–3.8 mmol/L]), time well below range (%TwBR; <54 mg/dL [<3.0 mmol/L]), glycemic coefficient of variation (CV), hypoglycemic events (i.e., values <70 mg/dL [<3.9 mmol/L] lasting ≥15 min), and nocturnal hypoglycemic events (i.e., hypoglycemic events between 10:00 p.m. and 08:00 a.m.), will be obtained from CGM software regardless of the brand used.

Data will be collected during continuous 14-day monitoring periods before the baseline and 12-week medical visits (36). For descriptive and exploratory purposes, CGM data will also be collected during the 7 days after each visit, corresponding to the period in which carbohydrate intake and insulin-correction doses are prospectively recorded (37).

Glycemic targets will be evaluated according to ADA guidelines (38): HbA1c <7%, CV ≤36%, TwAR <5%, TAR <25%, TIR >70%, TBR <4%, and TwBR <1%. The glycemic risk index (GRI) score will be calculated as follows: (3.0 × TwBR) + (2.4 × TBR) + (1.6 × TwAR) + (0.8 × TAR) (39).

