### Participant timeline

2.11

Each participant will follow a standardized timeline comprising screening and enrolment, baseline assessment, randomization, a 12-week intervention or usual-care period, post-intervention assessment, and post-T1 data collection. Screening and informed consent or assent may be initiated before the baseline visit.

Baseline procedures will be completed in the following sequence: (i) a baseline clinical visit, during which eligibility will be confirmed, informed consent or written assent will be verified, and sociodemographic, diabetes-related clinical, anthropometric, pubertal-maturation, and handgrip-strength data will be collected; (ii) central randomization immediately after the baseline clinical data have been entered into the Diactive-1 web platform; (iii) completion of the online web-based questionnaires within 48 hours after the baseline visit; (iv) a 7-day baseline data-collection period, during which participants will undergo fasting blood and urine testing and upload all available glucose-monitoring, insulin, and carbohydrate-intake data from their CGM system or insulin pump; (v) upload of the laboratory results and CGM or insulin-pump reports by the clinical research team within the following 72 hours, including glucose-monitoring data covering the 14 days before and 7 days after the baseline clinical visit; and (vi) verification of the completeness of all baseline information, followed by activation of the Diactive-1 app for participants allocated to the intervention group. Thus, intervention exposure will begin only after all baseline assessments and data-collection procedures have been completed and verified. The 12-week intervention or usual-care follow-up period will begin on the date of app activation or the corresponding date for participants allocated to usual care. To facilitate scheduling of the final clinical assessment, the web platform will generate automated alerts 15 and 7 days before the expected Week 12 assessment.

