### Data monitoring

2.14

Data and safety monitoring will be performed by the principal investigator and coordinating center throughout the trial. Monitoring will include remote review of recruitment and follow-up status, informed consent documentation, data completeness and consistency, adverse event records, app-recorded safety information, and adherence to intervention and assessment procedures. Deviations or data-quality issues will trigger documented corrective actions. The Diactive-1 web portal will provide a timestamped audit trail of relevant user actions, enabling remote verification of data integrity and site compliance. No formal data monitoring committee will be established, as the intervention is low-risk, non-pharmacological, and conducted alongside standard clinical care. Safety monitoring will remain independent of the funder, and any potential conflicts of interest will be disclosed in the “Funding” and “Conflicts of Interest” sections.

No interim efficacy analyses or formal stopping rules have been planned. However, if safety concerns, recurrent serious adverse events, or protocol-related risks are identified, the principal investigator may recommend temporary suspension, protocol amendment, or early termination of the trial. Any such decision will be documented and reported to the relevant ethics committee and institutional bodies in accordance with applicable regulations and local procedures.

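### CGM hypoglycemia is collected only for days 71–84 of the 84-day intervention, plus an exploratory week afterwards, so start-up has no objective comparison made the same way in both arms

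*Protocol article*

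**What the plan says.** **CGM windows.** Section 2.10.1 lists the CGM measures, among them time below range (TBR), time well below range (TwBR), hypoglycemic events ("values <70 mg/dL [<3.9 mmol/L] lasting ≥15 min") and nocturnal events. On timing it says: "Data will be collected during continuous 14-day monitoring periods before the baseline and 12-week medical visits". For descriptive and exploratory use, "CGM data will also be collected during the 7 days after each visit". Section 2.11 repeats this for the baseline upload, "including glucose-monitoring data covering the 14 days before and 7 days after the baseline clinical visit", and has the Week 12 procedures follow the baseline ones.

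**Start of exposure.** Section 2.11 states that "The 12-week intervention or usual-care follow-up period will begin on the date of app activation" (or a matching date in usual care) and that "intervention exposure will begin only after all baseline assessments and data-collection procedures have been completed and verified".

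**Load.** Section 2.8.3: "Load progression is organized into sequential ten-session blocks".

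**Other hypoglycemia information.** In the intervention arm, participants enter a glucose value before and after each session (section 2.8.3). Values and trend arrows are stored for completed sessions (section 2.10.17). When the app is reopened after a completed session, it asks about hypoglycemia since that session (section 2.12). In both arms, adverse events are gathered at visits, from participant or guardian reports and from team contacts (section 2.12).

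**Oversight.** Section 2.14: "No formal data monitoring committee will be established, as the intervention is low-risk, non-pharmacological, and conducted alongside standard clinical care". The coordinating center reviews adverse events and app safety data remotely, and section 2.16 adds a weekly review of trial conduct.

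**The concern.** The introduction names fear of hypoglycemia as a primary barrier to exercise and links it partly to insulin not being adjusted well around exercise. The discussion says that the effect of muscle contraction on glucose uptake may last for several hours. On that reasoning, the events of interest include delayed and overnight ones, and the first weeks, when participants are learning to adjust, are a plausible time for them.

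CGM measures such events in the same way in both arms, and every participant must use it (section 2.3). Yet the windows fall before exposure, at its end, and just after it. A participant who stopped training in week 5, perhaps because of hypoglycemia, would contribute a Week 12 window with no training in it. The trial could then report no difference in CGM hypoglycemia from data that cannot show an early one.

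**Working it through.** **1. Placing the windows.** Day 1 is app activation or the matching usual-care date. The period is 12 × 7 = 84 days. I assume that the final visit falls at the end of week 12; a later visit moves the window later.

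| Window | Position |
|---|---|
| 14 days before baseline visit | before exposure |
| 7 days after baseline visit | before exposure (activation follows completed baseline collection) |
| 14 days before Week 12 visit | days 71–84 |
| 7 days after Week 12 visit | after day 84, exploratory |

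Covered: 14/84 = 16.7%. Not covered: 70/84 = 83.3%, days 1–70, in both arms. Counting the exploratory week, when intervention participants still have the app and usual-care participants do not, gives 21 comparative days out of 84 + 7 = 91, or 23.1%. Days 1–70 stay empty either way.

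**2. What exists for days 1–70.**

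| Source | Intervention | Usual care | Limit |
|---|---|---|---|
| Session glucose and trend arrows | yes | no | typed-in spot values, stored for completed sessions; cannot show overnight events |
| App hypoglycemia question | yes | no | self-report, asked only on reopening after a completed session |
| Adverse-event reporting | yes | yes | unblinded report |
| Routine glucose review | yes | yes | not standardized across sites; not stated as a trial data source |

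No row is both objective and collected in the same way in both arms. The two app rows also end when a participant stops using the app, so they can be missing because of the harm itself.

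**3. Load steps relative to the window.** Sessions are assumed evenly spaced at f per week, so session s falls on day floor((s − 1) × 7/f) + 1. New blocks begin at sessions 11, 21, 31 and so on. The protocol gives only two anchors for f: the cited recommendation of at least 3 days a week and the per-protocol minimum of 2.

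| f | Days on which new blocks start | Before day 71 |
|---|---|---|
| 2 | 36, 71 | 1 of 2 |
| 3 | 24, 47, 71 | 2 of 3 |
| 4 | 18, 36, 53, 71 | 3 of 4 |
| 5 | 15, 29, 43, 57, 71 | 4 of 5 |

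The share of load steps outside the window is half at 2 sessions a week and two thirds or more at 3 to 5. The progression figure is not available, so this is indicative.

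**4. Illustration of a missed early excess.** The protocol gives no event rates. Assume a constant control rate, a rate ratio R in weeks 1–4 and 1.0 afterwards. The 12-week ratio is (4R + 8 × 1.0)/12.

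- R = 1.25: (5 + 8)/12 = 1.08
- R = 1.5: (6 + 8)/12 = 1.17
- R = 2.0: (8 + 8)/12 = 1.33

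In each case the ratio in days 71–84 is 1.00.

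**The case against.** The best defense is that glycemic stability is a secondary change-from-baseline outcome, for which two matched 14-day windows are coherent, and that the protocol announces no formal hypoglycemia conclusion such as non-inferiority. Both points stand, and the windows should not be replaced. They do not settle how harms are compared between arms.

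A reader might infer that hypoglycemia in the first ten weeks is never checked objectively. The documents do not support that. Glucose values and trend arrows are recorded around completed sessions from the first one, and the app does not permit training below 70 mg/dL. The gap is in the comparison between arms, not a total absence of data.

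A reader might also infer that the low-risk premise behind having no monitoring committee goes untested for ten weeks. That goes too far: adverse events are followed throughout (section 2.12), app safety data are reviewed (section 2.14), and trial conduct is reviewed weekly (section 2.16). A download at Week 12 would not change real-time oversight in any case.

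Saying that most load increases are missed depends on an assumed session frequency and fails at 2 sessions a week.

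Section 2.11 mentions uploading all available glucose data, which might suggest wider coverage. The same section then specifies reports for 14 days before and 7 days after the visit, and section 2.10.1 ties the outcomes to those windows.

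Finally, the previous trial of 62 participants had no reported hypoglycemic events (introduction), so the early excess above is hypothetical. That is fair. It limits how likely the problem is, but that was one setting and an earlier app version, and the present trial is meant to test transfer to other settings.

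**Conclusion.** The concern holds as a gap in comparative safety data. CGM-derived hypoglycemia is available for 14 of 84 intervention days (16.7%), plus an exploratory week after Week 12. For days 1–70, no objective measure is collected in the same way in both arms, and the app-based sources exist only in the unblinded intervention arm and only around completed sessions. An early, transient or training-ending excess could be absent from the between-arm comparison.

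The coverage figures follow from the stated windows and assume only that the final visit falls at the end of week 12. The rate ratios are illustrations under assumed values, and the documents give no evidence that such an excess will occur. The glycemic change outcomes are not in error. This is an inexpensive improvement to the safety comparison.

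**What to change.** - Keep the 14-day windows for the key secondary glycemic outcomes.
- Add to sections 2.10.1 and 2.11 that, at Week 12, the site also downloads CGM reports in both arms for the time from app activation (or the matching usual-care date) to Week 12, split into weeks 1–4, 5–8 and 9–12.
- Prespecify a descriptive safety comparison by arm and period: CGM wear time, TBR, TwBR and, where the device software supplies them, hypoglycemic and nocturnal events. Include participants who stopped training, as randomized.
- Treat linkage of events to session times as optional, where timestamped data exist. Section 2.6 describes PDF uploads, and the documents do not show that these would support linkage.
- State that the comparison serves the end-of-trial safety conclusion and is not real-time monitoring.

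**Cost.** A longer date range on reports that sites already produce, and one safety table. Files will be larger, and stored data may have device-dependent gaps, which the wear-time rows would show. No added visit, device or participant is needed. The change should be in place before Week 12 downloads begin.

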#### Twenty-four-hour movement behaviors

2.10.8

*Physical activity:* Self-reported physical activity will be assessed using the Spanish versions of the Physical Activity Questionnaire for Children (PAQ-C) (47), and the PAQ for Adolescents (PAQ-A) (48), according to participants’ age. Children aged 8–12 years will complete the PAQ-C, while adolescents aged 13–17 years will complete the PAQ-A. Both questionnaires are self-administered 7-day recall instruments designed to estimate general moderate-to-vigorous physical activity. The Spanish PAQ versions have shown good test–retest reliability and reasonable criterion validity against accelerometer-derived physical activity.

The PAQ-C comprises 10 items, nine of which contribute to the global score and assesses leisure-time activity, physical education, recess, lunchtime, after-school and evening activity, weekend activity, overall weekly activity, and daily activity frequency. The PAQ-A comprises 9 items, eight of which are scored, and assesses the same domains except recess, which is omitted. In both questionnaires the final item identifies illness and is not scored.

Scored responses will be coded from 1 to 5, with higher values indicating higher physical activity. The leisure-time domain will be computed as the mean of the listed activities, and the daily-frequency domain as the mean of the seven weekday scores. Original PAQ scores will be calculated as the mean of all scored domains: nine for the PAQ-C and eight for the PAQ-A, as the adolescent version omits the recess domain. To harmonize both questionnaires, a common PAQ score will be derived from the eight shared domains.

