#### Adherence to Mediterranean diet

2.10.14

To evaluate adherence to the Mediterranean diet, the Mediterranean Diet Quality Index for Children and Teenagers (KIDMED) index will be applied (58). This test was previously validated (58), and widely used in the Spanish young population with diabetes (59). The KIDMED index ranges from 0 to 12 and is based on a 16-question test. Items reporting unhealthy characteristics are scored with −1 point, and those reporting healthy characteristics with +1 point. The sum of scores will be used to categorize into 3 levels: (a) optimal Mediterranean diet (>8 points), (b) improvement needed (4 to 7 points), (c) low diet quality (≤3 points).

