Moreover, participants will be classified as responders or non-responders according to prespecified thresholds based on clinical guidelines (38), or minimally relevant standardized effect sizes (71), with the direction of beneficial response defined separately for each outcome. Response prevalence will be calculated by treatment group and compared using the χ² test. Additional longitudinal models may include responder status interaction to explore whether intervention effects differ between responder categories. To identify baseline profiles associated with response, exploratory regression models will be fitted. These analyses will be considered hypothesis-generating.

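### Three classification rules do not close: the CGM target limits do not fit the separate glucose bands they are applied to, a KIDMED score of 8 has no category, and age 18 has no physical-activity questionnaire (minor)

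*Protocol article*

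**What the plan says.** **CGM bands and targets (Protocol article, 2.10.1).** The section sets out separate glucose bands. The two high bands are "time well above range (%TwAR; >250 mg/dL [>13.9 mmol/L" and "time above range (%TAR; 180–250 mg/dL [10.1–13.9 mmol/L". The two low bands are "time below range (%TBR; 54–70 mg/dL [3.0–3.8 mmol/L" and "time well below range (%TwBR; <54 mg/dL [<3.0 mmol/L". Time in range (TIR) is 70–180 mg/dL. The same labels then receive targets, with a guideline of the American Diabetes Association as the source: "TwAR <5%, TAR <25%, TIR >70%, TBR <4%, and TwBR <1" (percent). The section also gives the GRI, which weights TwBR, TBR, TwAR and TAR by 3.0, 2.4, 1.6 and 0.8.

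**Responders (2.15).** Participants are to be "classified as responders or non-responders according to prespecified thresholds based on clinical guidelines", citing the same guideline, or by minimally relevant standardized effect sizes from another source.

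**KIDMED (2.10.14).** The index has sixteen items scored +1 or −1 and a stated range of 0 to 12. The levels are "a) optimal Mediterranean diet (>8 points), (b) improvement needed (4 to 7 points), (c) low diet quality (≤3 points".

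**Physical activity (2.10.8, against 2.3).** Eligibility covers ages 10 to 18. The questionnaire rule is "Children aged 8–12 years will complete the PAQ-C, while adolescents aged 13–17 years will complete the PAQ-A".

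**The concern.** These are rules that the protocol states, not details left for later. Followed literally, each one leaves some identifiable participants with a doubtful label or none.

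- For CGM, the same label serves as a band that excludes the extreme and as the quantity judged against a target. If the limit was set for all time above 180 mg/dL, applying it to 180–250 mg/dL alone makes the target easier to meet. At stake are target-attainment proportions within a key secondary outcome family (2.10), and any responder class that uses these limits.
- For KIDMED, one attainable score has no diet category.
- For physical activity, participants aged 18 have no assigned instrument. A questionnaire that is not given cannot be recovered afterwards.

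**Working it through.** **1. CGM limits against the TIR target.** Inputs, all from 2.10.1: TwAR <5, TAR <25, TIR >70, TBR <4, TwBR <1 (percent). The five bands cover all CGM time, so TIR = 100 − (total out-of-range time). TIR >70 therefore means less than 30% out of range. The sum of the out-of-range limits depends on how TAR and TBR are read:

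| TAR | TBR | Sum of limits | TIR if all are met | Implies TIR >70? |
|---|---|---|---|---|
| separate band | separate band | 25 + 5 + 4 + 1 = 35 | >65 | no |
| separate band | all <70 | 25 + 5 + 4 = 34 | >66 | no |
| all >180 | separate band | 25 + 4 + 1 = 30 | >70 | yes, exactly |
| all >180 | all <70 | 25 + 4 = 29 | >71 | yes |

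The first row is the protocol as written. Both rows that agree with TIR >70 need a cumulative TAR. TBR may be read either way.

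*Example A.* TAR 24, TwAR 4, TBR 3.5, TwBR 0.8. All four out-of-range targets are met as written. Total out of range = 32.3, so TIR = 67.7 and the TIR target is missed. Time above 180 = 24 + 4 = 28.

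*Example B.* TAR 24, TwAR 4, TBR 1, TwBR 0. Total out of range = 29, so TIR = 71 and all five targets are met as written. Time above 180 is again 28, which fails a 25% limit on all time above 180.

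With separate bands, the two high-glucose targets together tolerate up to 25 + 5 = 30% above 180 mg/dL, against 25% if TAR is cumulative: a difference of 5 percentage points.

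**2. KIDMED.** Checking the integers 0 to 12 against the three rules: 0–3 are low, 4–7 need improvement, 9–12 are optimal, and 8 is in none. On the range: if the maximum is 12 with items worth +1 or −1, there are 12 positive items and 16 − 12 = 4 negative ones, so the raw sum runs from −4 to 12. Any negative score still falls in the lowest category.

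**3. Physical-activity questionnaire.** Checking ages 10 to 18: 10–12 take the PAQ-C, 13–17 take the PAQ-A, and 18 has no version. If the upper age limit means up to the 18th birthday, the gap remains for participants aged 17 at baseline who turn 18 before the Week 12 assessment.

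**The case against.** The strongest reply is that targets judged one at a time need not add up. A participant with 35% out of range simply fails the TIR target listed beside the others, and the protocol defers to a guideline that is not at hand. This stands in part: the mismatch is a strong inference from the protocol's own figures, not proof of a departure from the guideline. It does not remove the point, because Example B passes every target, TIR included, while spending 28% of time above 180 mg/dL.

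A reader might infer that the TBR limit is too lenient too, so that attainment of the low-glucose target is overstated (up to 4 + 1 = 5% below 70 mg/dL rather than 4%). The documents do not support that. With TAR cumulative and the two low bands separate, the limits total exactly 30%, so the arithmetic does not settle the meaning of TBR.

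A reader might also infer that responder status is built on these limits. Section 2.15 does not say so. It points to guideline-based thresholds or standardized effect sizes, set separately for each outcome, and calls the analyses hypothesis-generating.

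On the other two gaps, it is fair to say that they are small. A KIDMED score of 8 keeps its numeric value and lacks only a label, the cut-off may be a one-character slip, and few participants may be 18 at an assessment. Diet and movement behaviors are exploratory (2.10). The gaps themselves are not in dispute.

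**Conclusion.** Wrong as written, with minor consequences.

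- **CGM targets.** The limits do not fit the separate bands: 35% allowed out of range against less than 30% under the TIR target. The figures point to a cumulative TAR and leave TBR open. This assumes that the limits were meant to be compatible with one another; the cited guideline must settle it. The same rule applies in both groups, so the direction of any effect on a between-group comparison is unknown.
- **KIDMED.** A score of 8 is unclassified; this is certain from the text. The stated 0–12 range does not match the scoring described, but it misclassifies no one.
- **PAQ.** Age 18 has no version; this is certain from the text. How many participants are affected cannot be derived from the protocol.

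The effect is confined to target attainment, any responder class that adopts these limits, the diet category, and one exploratory questionnaire at one age. The primary handgrip outcome, the continuous CGM outcomes and the GRI are unaffected.

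**What to change.** - **2.10.1.** Check the band definitions and limits against the cited guideline and state which quantity each limit applies to. For target attainment, and for any responder class using these limits, compute total time above 180 mg/dL, and total time below 70 mg/dL if the guideline defines TBR that way. Keep the separate bands for the GRI, whose formula weights each band once.
- **2.10.14.** Make the KIDMED categories cover every score, placing 8 by the validated source's cut-off, and reconcile the stated range with the scoring (raw sum −4 to 12).
- **2.10.8.** Name the PAQ version for participants aged 18 and for those who turn 18 before Week 12, for example the PAQ-A with the common eight-domain score already planned.

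The cost is a few lines of text. The first two changes use data already planned for collection. The third uses a questionnaire already in the trial, but should be made while recruitment is running (through September 30, 2026, section 2.4).
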